##### Missing Data Handling

Missing data will be analyzed considering their pattern and randomness following guidelines proposed by Schafer and Graham [93]. Bias due to systematic missing data will be managed according to guidelines proposed by Asendorpf et al [94].

##### Descriptives

Quantitative analyses will be conducted on an intention-to-treat basis. A flow diagram following the CONSORT guidelines will be included. Descriptive statistics will be calculated and presented. Independent samples’ t-tests and χ^2^ tests will be performed to check for baseline differences between the respective experimental conditions and the control condition with respect to demographic variables (eg, family status, age, gender, and level of education), time since end of treatment, and baseline levels of the outcome variables. If we find statistically significant differences in the mean of fatigue severity across baseline descriptives, dummy variables will be added to the model as covariates to control for these differences.

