#### Pre-Analysis

##### Power Analyses

The sample size for analyses for data relating to the primary objective has been calculated for a repeated measures analysis of variance: based on an alpha of .05, a minimal detectable effect size of f2=.15, and a power of .80, a total number of 55 participants [80] is required in each group to answer the primary research question of this study in a statistically valid manner.

We expect to be able to include 330 eligible participants within a period of 2 years, based on a mean of 3.7 intakes per week for the eMBCT of the Helen Dowling Institute in 2011. An estimated attrition of 30% of the participants during both experimental interventions and 15% during the minimal intervention control condition [51] would leave us with 77 participants in each experimental group and 94 participants in the control group at T2. Again, we expect a dropout rate of 30% during the second semester. Such a dropout would leave a total of 110 participants completing each experimental intervention. Ten percent of the participants may have to be excluded from the analyses because of recurrence or diagnosis of metastasis. That would result in 198 participants that complete the full trial. We expect that this number will be enough for testing the 6 mediating factors or effect predictors: A classical, conservative power calculation (analysis of variance for testing 6 mediators or effect predictors with an intermediate effect size (f2=.08), corrected according to Bonferroni (alpha=.05/6), and at a power of .80 [81]) would result in approximately 254 participants being needed. We expect that the actual power when including 198 participants, and not the required 254 participants, will be great enough to detect up to 6 mediators or effect predictors with the use of Bayesian statistics [76]. Bayesian statistics allow analysis on small sample sizes [76,77], as more power can be generated with the use of prior information which is incorporated in the model that is being tested. Various papers describe comparisons between traditional null hypothesis testing and Bayesian estimation [82-85]. For this study, prior knowledge is available for many parameters, such as the effects of mindfulness in cancer survivors [23,25,66,86] and the role of working alliance in online interventions [87]. Examples of these methods can be found in both applied psychology and social science articles [88-92].

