#### Core Analysis

##### Effectiveness

###### Overview

Five steps will be taken to evaluate the effectiveness of both interventions, which are explained here in a generic way. The specific hypotheses on the effectiveness of the interventions in our study are shown in Textbox 1.

Hypotheses on effectiveness.
*Primary outcome*
In both experimental conditions:Fatigue severitydecreases during the intervention, andremains decreased after 6 months.After 6 months, fatigue severity has decreased significantly more compared to the control condition.After 6 months, more participants show a clinically relevant reduction of fatigue severity compared to the control condition. A patient is considered clinically improved if he or she has a reliable change index of more than 1.96, according to the reliable change index, and the end score has to be within the normal range, that is a score < 1 standard deviation above the mean of a normative group [94] (ie, a score < 30.4 on the CIS fatigue severity subscale [51]).
*Secondary outcomes*
For both interventions we expect that:After 6 months, mental health and work ability have improved more than in the control condition.After 12 months, fatigue severity, work ability, and mental health remain improved in both intervention groups.Improvements in mental health and work ability after 6 and 12 months are related to reductions in fatigue severity.Return to work and reduced absenteeism will be studied as explorative outcomes.

###### Step 1

Overall effectiveness will be tested in an intention-to-treat analysis by a multiple group latent growth model [79] using data from the first semester. This technique allows individuals to have an individual growth trajectory over time and compensates for missing data in an elegant way.

Since different growth patterns are expected for the pre-intervention period, the intervention period, and the post-intervention period, we will apply piecewise growth modeling so that a slope factor will be estimated for each of the 3 periods (Figure 4). Initial intercepts will be configured to represent the T0b score. This intercept and the pre-intervention slope factor will be constrained to be equal between all 3 conditions (and this assumption will be checked), whereas the subsequent slope factors will be estimated separately for the 3 conditions.

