The fit of the piecewise model will be compared with a quadratic model. In the quadratic model, the entire first semester is modeled with 1 slope factor and 1 quadratic factor for each of the 3 conditions and an intercept that represents T0b and is constrained similarly to the piecewise model.

Both models will be run both with and without using time-varying loadings in order to check whether corrections should be made for differences in timings between the questionnaires. Growth factor estimates and model fits for all 4 models will be reported (Table 5).

Neither the participants nor the researchers ([name] and MW) are blinded to allocation. Therefore, an independent statistician ([name]) who is blind to the allocation will test the primary hypothesis.

The same procedure will be followed for the secondary outcomes, except that the initial intercept of mental health will represent T0a, rather than T0b, because T0b does not include an assessment of mental health.

Results of frequentist analyses will be reported by *P*-values (significant in case <.05) and with 95% confidence intervals. Parameter estimates of models by means of Bayesian estimators will be reported with 95% central credibility intervals.

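### Significance tests on the trial data decide whether covariates enter the primary model, and the triggering sentence can be read in two ways, so the primary model is not fixed in advance

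*Protocol article*

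**What the plan says.** All references are to the protocol article.

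- **Descriptives (Pre-Analysis).** t-tests and chi-square "tests will be performed to check for baseline differences between the respective experimental conditions and the control condition". They cover "demographic variables (eg, family status, age, gender, and level of education), time since end of treatment, and baseline levels of the outcome variables".
- **The covariate rule, same section.** "If we find statistically significant differences in the mean of fatigue severity across baseline descriptives, dummy variables will be added to the model" as covariates. This is the only rule for covariates in the effectiveness analysis.
- **Step 1 (Effectiveness).** The primary analysis is a multiple-group latent growth model. It lists no covariates. The intercept is set to represent T0b fatigue, and it and the pre-intervention slope are "constrained to be equal between all 3 conditions (and this assumption will be checked"). Frequentist results count as "significant in case <.05".
- **Table 3.** Age, gender, education, time since previous treatment, fatigue duration and comorbidity are all collected at T0a.
- **Textbox 3 and Step 8.** Education, time since last treatment and comorbidity are among the expected predictors of the interventions' effect on fatigue. They are used in the effect-predictor steps and not as fixed terms in Step 1.
- **Principal Findings (Discussion).** The article states that every method is now openly fixed beforehand.

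**The concern.** The article states a covariate rule, so this is not a detail left to a fuller document. The rule makes the form of the primary model depend on preliminary tests of the trial's own data.

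Two things are at stake. The first is pre-specification. The wording of the trigger is ambiguous, so two analysts following it in good faith could fit different primary models, and neither could name the covariates beforehand. The second is precision. If the gate looks at differences between arms, it responds to chance imbalance and not to how strongly a variable predicts later fatigue. A useful covariate is then left out most of the time. Allocation is by simple randomisation with no stratification described (Randomization section), so the design itself does nothing to balance such variables.

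**Working it through.** The plan gives no figure for the effect of this rule, so there is none to reproduce directly. The check uses the plan's expected group sizes, which do reproduce: 330 / 3 = 110 per arm; 110 × 0.70 = 77 in each experimental arm; 110 × 0.85 = 93.5, given as 94, in control at T2 (Power Analyses).

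**1. The two readings of the trigger**

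- *Reading A: mean baseline fatigue differs between arms.* Each experimental arm is tested against control, giving 2 tests at .05 (two-sided assumed). Under proper randomisation the chance of at least one flag is 1 − 0.95² = 0.0975, about 10%. This treats the tests as independent. The shared control arm makes it an approximation, slightly on the high side.
- *Reading B: fatigue differs across levels of a baseline characteristic such as gender or education.* This screens for association with fatigue. The null is not known to be true, so no chance rate can be given.

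Under A, adjustment happens in about one properly randomised trial in ten, for reasons of chance. The dummies would also address an arm difference that Step 1's equal-intercept constraint already sets to zero. Under B, the covariates are whichever characteristics reach significance in this sample. In neither case can the set be written down today.

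**2. What an arm-difference gate does to power and type I error**

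Inputs: 77 versus 94 participants (plan); one standardised baseline covariate with outcome correlation ρ (not given in the article, assumed 0.3, 0.5, 0.7); true effect 0 or 0.4 SD (assumed); two-sided .05; 8,000 simulated trials per setting. Three rules were compared: never adjust; adjust only if the covariate differs between arms at p < .05; always adjust.

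| ρ | Power, never | Power, gated | Power, fixed | Type I, gated | Type I, fixed |
|---|---|---|---|---|---|
| 0.3 | 0.73 | 0.74 | 0.77 | 0.048 | 0.051 |
| 0.5 | 0.73 | 0.74 | 0.84 | 0.039 | 0.049 |
| 0.7 | 0.74 | 0.76 | 0.96 | 0.038 | 0.051 |

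The gate fired in 4.4% to 5.2% of trials whatever the value of ρ. That is why it recovers so little.

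**3. Hand check of the ρ = 0.3 row**

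- SE of the difference in SD units: √(1/77 + 1/94) = √(0.01299 + 0.01064) = 0.1537.
- Unadjusted: 0.4 / 0.1537 = 2.602. With a critical value of about 1.974, power ≈ Φ(2.602 − 1.974) = Φ(0.628) ≈ 0.735.
- Fixed adjustment multiplies the SE by √(1 − 0.3²) = 0.954. Then 2.602 / 0.954 = 2.728, and power ≈ Φ(0.754) ≈ 0.775.

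Both agree with the simulation.

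**4. Which row is relevant**

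T0b fatigue, probably the strongest predictor of later fatigue, is in the Step 1 model whatever the gate does. What remains is the contribution of the other covariates, so the ρ = 0.3 row is closer to this trial than the lower rows.

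**5. Limits of the simulation**

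It is a two-group linear model with one covariate and not the latent growth model. It gates on that covariate's own arm difference, so it shows how an arm-difference gate behaves in general. It says nothing about Reading B, where a characteristic related to fatigue has a better chance of being selected and the precision loss could be smaller.

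**The case against.** The strongest reply is that the harm is small and that several tempting extensions fail. Most of this stands.

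- **Chance of a flag.** A reader might count six screened variables and two comparisons, obtain 1 − 0.95¹² = 0.46, and call the choice of model a coin toss. The text does not support this. The trigger concerns mean fatigue severity, not any baseline variable that differs between arms. Neither reading yields twelve null tests.
- **Irrelevant covariates.** The complaint that the rule ignores prognostic importance applies to Reading A. Under Reading B, selection is by association with fatigue.
- **Error rate.** A reader might infer that the preliminary test inflates the .05 level. In the simulation the gated rule gave 0.038 to 0.048, which is at or below nominal.
- **The equality check in Step 1.** This could be taken for a second data-driven switch. The article says only that the assumption is checked and states no change of model. A check also has some purpose here: the Results section reports an allocation error in 2014, and participants who do not complete T0c after learning their allocation are not counted as included.
- **Arm sizes.** The January 2015 sizes of 36, 24 and 32 might be read as evidence of imbalance. Unequal numbers do not show covariate imbalance, and the allocation error, which sent 10 participants directly to AAF, explains part of them.
- **Dummy variables.** These need not mean that age or time since treatment will be categorised. The article does not say so.
- **Choice of covariates.** Textbox 3 lists predictors of intervention effect, not prognostic main effects, so the set remains a judgement for the trial team.

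None of this makes the rule determinate. Both readings still let a significance test on trial data choose the covariates.

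**Conclusion.** The point holds in a limited form. The primary model's covariate set is not fixed, because it depends on a significance test whose trigger is ambiguous. This conflicts with the article's own claim that all methods are settled in advance.

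Under the arm-difference reading, the gate would fire in about 10% of properly randomised trials and would recover almost none of the precision available from fixed adjustment. The likely cost is modest: about 0.03 in power (0.74 against 0.77), assuming ρ = 0.3, an effect of 0.4 SD and the planned 77 versus 94. It would be larger only if the other covariates predicted fatigue more strongly than that, which the article does not establish.

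The documents do not support a claim of inflated type I error, a near-even chance of switching models, or demonstrated imbalance between the arms.

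**What to change.** Rewrite the Descriptives paragraph and add one sentence to Step 1:

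- Keep the baseline table as description, and remove significance testing as the trigger for adjustment.
- Name now a short set of covariates already collected. Education, time since last treatment and comorbidity are natural candidates because Textbox 3 expects them to matter; age and gender can be added if wanted. Enter variables as continuous where they are measured so, and include the set whatever the observed balance.
- Keep T0b fatigue through the equal-intercept constraint, and report the equality check as a diagnostic.
- Report the unadjusted model as a sensitivity analysis.

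The cost is one paragraph of wording and a few degrees of freedom. The article says it was submitted before any data were analysed, so at that stage the set could be chosen without knowledge of results.

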#### Core Analysis

##### Effectiveness

###### Overview

Five steps will be taken to evaluate the effectiveness of both interventions, which are explained here in a generic way. The specific hypotheses on the effectiveness of the interventions in our study are shown in Textbox 1.

Hypotheses on effectiveness.
*Primary outcome*
In both experimental conditions:Fatigue severitydecreases during the intervention, andremains decreased after 6 months.After 6 months, fatigue severity has decreased significantly more compared to the control condition.After 6 months, more participants show a clinically relevant reduction of fatigue severity compared to the control condition. A patient is considered clinically improved if he or she has a reliable change index of more than 1.96, according to the reliable change index, and the end score has to be within the normal range, that is a score < 1 standard deviation above the mean of a normative group [94] (ie, a score < 30.4 on the CIS fatigue severity subscale [51]).
*Secondary outcomes*
For both interventions we expect that:After 6 months, mental health and work ability have improved more than in the control condition.After 12 months, fatigue severity, work ability, and mental health remain improved in both intervention groups.Improvements in mental health and work ability after 6 and 12 months are related to reductions in fatigue severity.Return to work and reduced absenteeism will be studied as explorative outcomes.

###### Step 1

Overall effectiveness will be tested in an intention-to-treat analysis by a multiple group latent growth model [79] using data from the first semester. This technique allows individuals to have an individual growth trajectory over time and compensates for missing data in an elegant way.

Since different growth patterns are expected for the pre-intervention period, the intervention period, and the post-intervention period, we will apply piecewise growth modeling so that a slope factor will be estimated for each of the 3 periods (Figure 4). Initial intercepts will be configured to represent the T0b score. This intercept and the pre-intervention slope factor will be constrained to be equal between all 3 conditions (and this assumption will be checked), whereas the subsequent slope factors will be estimated separately for the 3 conditions.

The fit of the piecewise model will be compared with a quadratic model. In the quadratic model, the entire first semester is modeled with 1 slope factor and 1 quadratic factor for each of the 3 conditions and an intercept that represents T0b and is constrained similarly to the piecewise model.

Both models will be run both with and without using time-varying loadings in order to check whether corrections should be made for differences in timings between the questionnaires. Growth factor estimates and model fits for all 4 models will be reported (Table 5).

Neither the participants nor the researchers ([name] and MW) are blinded to allocation. Therefore, an independent statistician ([name]) who is blind to the allocation will test the primary hypothesis.

The same procedure will be followed for the secondary outcomes, except that the initial intercept of mental health will represent T0a, rather than T0b, because T0b does not include an assessment of mental health.

Results of frequentist analyses will be reported by *P*-values (significant in case <.05) and with 95% confidence intervals. Parameter estimates of models by means of Bayesian estimators will be reported with 95% central credibility intervals.

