#### Eligibility

The following criteria are used to check eligibility for participation in the trial:

Completion of a curative-intent treatment for cancer at least 3 months ago (checked by participant’s medical doctor). For this study, surgery, chemotherapy, radiotherapy, immunotherapy, and/or stem cell transplantation are considered treatment. However, hormonal therapy, the use of anti-inflammatories, and monitoring visits are not considered treatment for this study.Patient has been suffering from severe fatigue for at least 3 months.Patient scores 35 or higher on the fatigue severity subscale of the Checklist for Individual Strength (CIS).Aged 19 years old or older.At least 18 years old at disease onset.Capable of reading and writing in the Dutch language and of using the Internet (implicit eligibility criterion accounted for during registration, but not checked explicitly).

If patients meet 1 or more of the following criteria, they are excluded from participation:

Indication of current disease or tumor activity (checked by the participant’s medical doctor).Current or former severe psychiatric morbidity, for example, major depression, psychosis, or schizophrenia (checked by the participant’s medical doctor).Being dependent on a wheelchair for daily activity (self-report).Recurrence of cancer during the course of the study (self-report).Current substance abuse, except for smoking.Previously attended the eMBCT of the Helen Dowling Institute.

In addition to the mentioned exclusion criteria, please note that:

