### Outcome Measures

#### Fatigue

Fatigue severity will be assessed with the CIS, which consists of 20 items that score on a 7-point Likert scale [53,54]. The CIS has 4 subscales (fatigue severity, motivation, concentration, and physical fatigue) of which the fatigue severity subscale will be used as the primary outcome (8 items, range: 8-56 points). The CIS has shown good discriminative validity in a working population [55], is sensitive to changes in the chronic fatigue syndrome population [56], and has previously been used with cancer survivors [7,57]. The CIS strongly resembles the Multidimensional Fatigue Inventory, which is often used in international studies [54]. Fatigue severity will be assessed at T0a, T0b, M3, M6, M9, T1, T2, and T3. However, the other 3 subscales will only be assessed at T0b, T1, T2, and T3.

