**Figure 4 figure4:**
[figure not shown]
Simplified representation of a piecewise linear latent growth model, with latent intercept factor (I), latent slope factors preintervention (S(pre)), during the intervention (S(int)), and postintervention (S(post)), and 7 indicators Y. Error terms, correlation coefficients, and covariances are left out.

**Table 5 table5:** Growth factor estimates of 4 different latent growth models.

	Fixed loadings	Time-varying loadings
Piecewise, linear	Mean: I, S(pre), S(int), S(post) Variance: I, S(pre), S(int), S(post)	Mean: I, S(pre), S(int), S(post) Variance: I, S(pre), S(int), S(post)
Quadratic	Mean: I, S, Q Variance: I, S, Q	Mean: I, S, Q Variance: I, S, Q

###### Step 2

The effect size of both experimental interventions will be calculated according to recommendations in Feingold (2009) [95] for both primary and secondary outcomes.

###### Step 3

The proportion of participants who make clinically relevant progress on the primary outcome will be calculated for all 3 conditions; again, in an intention-to-treat analysis. Percentages and standard deviations of the reliable change index will be presented.

###### Step 4

A latent growth model will be built of the primary outcome, in which the outcome measures that have been measured at T3 will also be included, as distal outcomes of changes in the primary outcome during the first semester.

###### Step 5

A growth mixture model (GMM) will be used to further explore differences between individuals, and more specifically to identify subpopulations (latent classes) with homogeneous growth trajectories of the primary outcome within the experimental groups. The Bayesian information criterion will be used for model selection [96].

If convergence considerations allow, this model will be adjusted to allow covariance of the growth factors in order to acknowledge individual variation around the estimated growth trajectories. The trace plots will be inspected to check whether the models have converged to global solutions and a set of diverse starting values will be used. For more information on these analyses, we refer to an introduction to GMM and latent class growth analysis by Jung and Wickrama [97] and examples of similar analyses in the field of Internet interventions [98] and cancer patients [41].

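### In the fixed-loading piecewise model, the promised S(pre) variance cannot be separated from T0a error, and Step 1 states no restriction that would allow it

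*Protocol article*

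**What the plan says.** The Fatigue section under Outcome Measures gives the occasions: "Fatigue severity will be assessed at T0a, T0b, M3, M6, M9, T1, T2, and T3". Step 1 of the effectiveness analysis works by "using data from the first semester", which drops T3 and leaves seven scores. This agrees with the Figure 4 caption, which names "latent slope factors preintervention (S(pre)), during the intervention (S(int)), and postintervention (S(post)), and 7 indicators Y".

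On the form of the model, Step 1 says "we will apply piecewise growth modeling so that a slope factor will be estimated for each of the 3 periods (Figure 4". On coding, it states "Initial intercepts will be configured to represent the T0b score", and then "This intercept and the pre-intervention slope factor will be constrained to be equal between all 3 conditions". The later slopes are estimated separately by arm.

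Table 5 promises, for the piecewise model with fixed and with time-varying loadings alike, "Variance: I, S(pre), S(int), S(post)". The fit of the piecewise model is to be compared with that of a quadratic model, and estimates and fit are to be reported for all four models.

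The Figure 4 caption notes that error terms and covariances are omitted from the drawing. The text does not say whether error variances are free or equal over time. Step 1 gives no restriction on the S(pre) variance and no fallback; the convergence proviso in Step 5 concerns the mixture model only.

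T0a is also the screening score. The entry criterion reads "Patient scores 35 or higher on the fatigue severity subscale".

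**The concern.** A random slope needs at least two occasions at which it moves the score, or else outside knowledge of the error variance. S(pre) has one such occasion. The spread of T0a around the intercept is then either true change before the intervention or measurement error at T0a, and the data cannot say which.

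This is the model for the primary outcome, and Step 8 builds on the final model of Step 1. If the listed model cannot be estimated, somebody must choose a restriction after the data are in. The usual restrictions are not interchangeable: they can change which of the piecewise and quadratic models fits better. The article presents its methods as fixed beforehand, and here they are not.

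The obvious restriction, equal error variances over time, has a weakness of its own. T0a was selected at 35 or higher, which shrinks its variance and pulls the implied S(pre) variance downward.

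**Working it through.** **Indicator count.** T0a, T0b, M3, M6, M9, T1 and T2 make 7, which reproduces the figure in the Figure 4 caption.

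**Loadings.** With the origin at T0b, T0b loads zero on every slope. S(pre) loads (−g, 0, 0, 0, 0, 0, 0), where g is the T0a–T0b interval. S(int) is taken to run from T0b to week 9 and S(post) from week 9 on, so that T1 and T2 both load on S(post). The week-9 break is my reading of the 9-week intervention period. A break at T1 would leave S(post) with T2 alone and raise the same question there.

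**Where the S(pre) variance appears.**

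Var(T0a) = Var(I) − 2g·Cov(I, S(pre)) + g²·Var(S(pre)) + θ(T0a)

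Var(S(pre)) and θ(T0a) occur in no other moment. The covariances of S(pre) are fixed by the covariances of T0a with the later scores. Only the sum g²·Var(S(pre)) + θ(T0a) can be estimated, whatever g is.

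**Rank of the Jacobian, covariance part.**
- Free errors: 4 variances + 6 covariances + 7 errors = 17 parameters, rank 16. With the 4 means, 21 and 20. The null direction involves only Var(S(pre)) and θ(T0a).
- Uncorrelated factors do not repair it (14 of 15, means included). Nor does equality across arms (52 of 53 with errors free by arm; 38 of 39 with errors shared).
- T0a error tied to T0b error: 16 of 16.
- All errors equal: 10 + 1 = 11 parameters, rank 11.
- S(pre) with a mean only, errors free: 3 variances + 3 covariances + 7 errors = 13 parameters, rank 13.
- Individually varying loadings, free errors: 21 of 21, means included, with assumed gaps of 2, 4, 6 and 8 weeks. Var(T0a) then changes with each person's g, which separates the two terms.

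**Equal errors when T0a is selected.** By the Results section, 60% of 50 exclusions were for a score below 35, that is 30, out of 111 + 50 = 161. The share cut off is 30/161 = 19%. Under a normal screening score the truncation point is z = −0.89 and the variance ratio 0.598, so the fractional loss is k = 0.40 (0.43 with 30/141).

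Let the true score be stable from T0a to T0b, with reliability r and unselected variance σ². After selection on T0a:
- Var(T0a) = (1 − k)σ²
- Var(I) = (r − r²k)σ²
- Cov(T0a, I) = r(1 − k)σ²
- error at the other occasions = (1 − r)σ²

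The implied pre-period variance is Var(T0a) − error + Var(I) − 2Cov(T0a, I) = −k(1 − r)²σ². At an assumed r = 0.8 this is −0.40 × 0.04 = −0.016σ². For r = 0.7 it is −0.036σ² and for r = 0.9 it is −0.004σ².

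**How often the estimate is negative** (equal errors, N = 330, assumed 4-week gap, reliability 0.8 to 0.6):

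| True pre-period variance, share of score variance | No selection | 19% cut at T0a |
|---|---|---|
| 0 | about 50% | 72% to 89% |
| 5% | 6% to 22% | 21% to 68% |
| 10% | 0% to 6% | 2% to 46% |
| 20% | 0% | 0% to 12% |

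With selection, the expected estimate is positive once the true variance exceeds about 2% (reliability 0.8) to 9% (reliability 0.6) of the score variance.

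**Effect on the contrast and on model choice.** In simulated fits with assumed values, changing the restriction moved the 6-month piecewise contrast by about 0.001 on average and by 0.04 at most, against a standard error of 0.135. The piecewise model beat the quadratic on BIC in 38%, 70% or 100% of trials, depending on the restriction. The quadratic contrast was −0.23 against −0.29. BIC served as the fit measure here; the article names it only for Step 5.

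**The case against.** Four points can fairly be made against this.

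- **The article never commits to free error variances.** Figure 4 is a simplified drawing, and residual structure is the kind of detail a condensed article leaves out. That is so, and the omission alone would be no finding. But Table 5 names a particular variance to be estimated, and the design described cannot deliver it with fixed loadings unless something is added. A reader might infer that both piecewise versions fail; the documents do not support that, because the time-varying version is formally identified when timings differ between people.

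- **The treatment effect is safe.** This stands. S(pre) is held equal across arms, and all means, as well as the variances of I, S(int) and S(post), are identified. A reader might infer that the primary comparison is invalid; it is not.

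- **Just-identifying restrictions all give the same fit.** True where the solution is admissible, as when only the T0a and T0b errors are tied. The other natural choices restrict more. Equal errors everywhere lowers the rank from 16 to 11, and a mean-only S(pre) lowers it from 16 to 13. Fit then changes, and so can the comparison with the quadratic model. Reporting all four models limits selective choice but does not fix which restriction is used.

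- **The negative-variance argument rests on assumptions.** Largely right. Reliability and true change are not in the article, and about half of estimates are negative without any selection when the true variance is zero. The article also expects a distinct pre-intervention pattern. A reader might infer that truncation at 35 makes an inadmissible result the usual outcome; that holds only if true change is small. A Bayesian prior would rule out negative values, but with free errors the prior would decide the split.

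**Conclusion.** The point holds for the fixed-loading piecewise model. The S(pre) variance listed in Table 5 is confounded with T0a's error variance (rank 16 of 17), and Step 1 states no restriction that separates them. This follows from the occasions and the coding in the article and needs no assumed value beyond the week-9 break between S(int) and S(post).

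The consequence is limited. The model cannot be estimated as tabulated, and the comparison with the quadratic model depends on a restriction chosen after the data are seen. The simulated 38%, 70% and 100% show that this can matter; their size rests on assumed values. The 6-month contrast within the piecewise model is little affected.

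Equal error variances would identify the model, but selection at T0a makes a negative S(pre) variance more likely when true change before the intervention is small. How often cannot be settled from the article. The change is worth making because it is cheap and closes a choice that should not be left open.

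**What to change.** In Step 1, state the error-variance structure and one restriction before analysis. Preferably give S(pre) a mean only, with its variance and covariances fixed at zero, and leave T0a's error variance free. This is identified (13 of 13), keeps the planned check that S(pre) is equal across arms, and does not force the selected T0a score to share an error variance with the other occasions. In Table 5, remove S(pre) from the variance list in the fixed-loading piecewise cell.

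Keep T0a as an indicator in both the piecewise and the quadratic model. Making it a covariate in the piecewise model alone would leave the two models describing different outcome sets, and their fit could no longer be compared.

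The cost is wording in Step 1 and one cell of Table 5; no data collection changes. The small downside is that no S(pre) variance is reported for that model.
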